#### D.3.4 Incentives

For the clinic practices in both study arms, CHICA will be provided free. Other incentives for control practices to participate in the study will include the provision of the “Autism and Pervasive Developmental Disorders Tool Kit” developed by the HANDS in Autism Project Team at the Christian Sarkine Autism Treatment Center located at Riley Hospital for Children in Indianapolis, Indiana. For children and parents in both study arms, a \$50 cash incentive will be provided after the completion of each assessment. Assessments will be conducted at 3 month intervals – baseline, 3 months, 6 months, 9 months, and 12 months. Therefore, the total incentive available to a study participant is \$250.

### **D.4 Sample Size (Aims 2 and 3)**

#### D.4.1. Sample Size Calculation for Aim 2

The primary outcome of interest for aim 2 is the proportion of children at the 18 or 24-month visits that will be screened for ASD using the M-CHAT in the intervention group and any ASD specific screening tool in the control group. Dosreis and colleagues found that while 82% of pediatricians reported screening for general developmental delays, only 8% screened for ASD. Though we do not anticipate much variability in this rate at our study clinics, we will use four different rates, 6%, 8%, 10% and 12%, at baseline to estimate intra-clinic correlation. This translates to an intra-class correlation coefficient 0.0041. However, for a conservative estimation of sample size, we will use intra-class correlation 0.0082, twice that of the correlation we estimated.

To be conservative, we will assume 10% of the children are screened for ASD under standard practice in our clinic sites. Based on pilot data involving a different universal screening tool in the pediatric population (i.e., the Ages and Stages Questionnaire), we expect at least 50% of the children at the 18 or 24-month visits will be screened in the intervention clinics. However, we will use a more conservative estimate, that is, 40% of the children will be screened using the M-CHAT.

Using a chi-square test and setting alpha at 0.05, the probability of detecting a statistically significant difference in the proportion of children screened at the 18 or 24-month visits between the intervention and the control group is 90% with an effective sample size of 49 per group. Hence, the total effective sample size ( $n^*$ ) is 98. The unit of randomization is the practice or clinic, but the unit of analysis is the individual patients. Since patients are nested within practice, responses from the patients within practice are likely to be correlated. This intra-cluster correlation must be taken into account in the calculation of sample size and in the analyses. We computed the number of patients per clinic,  $m$ , required for the study, using the following equation:

$$m = \frac{1 - \rho}{\frac{k}{n^*} - \rho}$$

where  $\rho$  = intra-practice correlation,  $k$  = number of clinics,  $mk$  = total sample size,  $n^*$  = total effective sample size =  $mk/DE$ , and  $DE$  = design effect =  $1 + \rho(m-1)$ 

Using 4 clinics and assuming intra-class correlation of 0.0082, we need to recruit 31 children per clinic. We anticipate that drop-out is not a major problem and unlikely to be more than 10% for the primary outcome. We will account for this factor by oversampling patients by 10%. According to our previous experience and data from the four clinics included in this study, at least 1000 patients present to these four clinic sites for 18 or 24-month visits each year, leading to 3000 patients if the study runs for 3 years.

#### D.4.1. Sample Size Calculation for Aim 3

For aim 3, children between the ages of 18 months through 5 years with newly diagnosed ASD will be included as potential participants. The primary outcome of interest for this aim is the number of activities/involvements (listed in Figure 9) that a child diagnosed with an ASD is receiving. Although better outcomes are expected in the intervention group, no preliminary data are available to support this hypothesis. Hence, the primary purpose of this study is to generate preliminary data on this outcome in order to design a large scale study. Even though the screening rate could be as low as 8% in the intervention group and 40% in the intervention group, the vast majority of children should still receive a diagnosis of ASD by age 5 even without standardized screening at the 18 or 24-month visits. It is likely that we will have at least 80% of the children with a diagnosis of ASD receiving care for that diagnosis by age 5. Though we do not know how many children with newly diagnosed ASD will be available in each of the four clinics, we anticipate more than 20 children in each of the two treatment groups assuming a prevalence of 1 in 150, successful identification of 80% of children with diagnosis ASD, and recruiting about 4000 per group. In 2007, the four study clinics saw 8,528 patients between ages of 0 and 3 years and 3,065 patients between the ages of 4 and 5. Hence, we do not anticipate any problem in having 4000 children per group for this study. We base the sample size justification on estimation and not hypothesis testing. A sample size of 20 per group can be considered adequate for a pilot study given that a sample size as low as 12 in each group provides adequate power for precision in estimating the difference between means in clinical trials in the sense that the gains in precision are less pronounced as sample size exceeds 12.

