Although randomization at the physician/patient level is sample-size efficient, we chose a cluster randomization by clinic because contamination is a major concern. If we randomize at the physician level, physicians in the same clinic who are assigned to different treatment arms might communicate regarding the CHICA system in terms of its operation and consequences, which could contaminate the control arm. If we randomize at the patient level, the on and off usage of the CHICA might confuse the physician and lead some to think that CHICA is malfunctioning. Anecdotally, this has been our experience with the asthma and maternal depression studies we have conducted. We have found previously that randomization at the patient level can lead to irritation and inconvenience for both physicians and clinic staff. The limitation of randomization at the clinic level is inflated sample size and potential bias caused by unknown characteristics that are differentially distributed in the four clinics and related to the outcome. Characteristics of this nature could include awareness of ASDs by physicians, socio-economic status of patients and so on. To our knowledge however, there is no reported significance and scale of the effect of these factors. After weighing the limitation and advantage of each option, we decide to allocate two clinics to each of the study arms. We will adjust for intra-cluster correlation and potential confounders in the analysis.

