#### D.3.4 Patient Recruitment and Consent

The same four clinics utilized in aim 2 of the study will be utilized for aim 3 of the study. The same two clinics that served as the intervention group in aim 2 will once again serve as the intervention group for this portion of the study. These two clinics will have the ASD care and management module as part of the CHICA system. The two control clinics will have the CHICA system but will NOT have the ASD care and management module.

For this portion of the study, consent will be obtained from those patients who are newly diagnosed with ASD so that we may collect additional evaluation and assessment data beyond that which is normally documented during standard care practices. Children and their parents will be recruited and consented through the Pediatric Research Network (PResNet). PResNet is a pediatric practice based research network located at the Indiana University School of Medicine (See full description in Resources section of the proposal). PResNet was established in 2006 as an offshoot of ResNet, the very successful practice-based research network of the Indiana University Medical Group. Since 2000, ResNet has been involved in more than 40 studies supported by over \$15 million in extramural grants. In these studies, ResNet has recruited more than 7,000 patients, approximately 68% of those patients contacted (a remarkable figure, considering that two-thirds of those approached were African-American or Hispanic). In 2006, PResNet was established to facilitate pediatric specific primary care research efforts. While it does not have as long of a track record of recruiting patients as ResNet, it follows the same processes and procedures and therefore has encountered the same level of success at patient recruitment. PResNet has been involved with 8 studies in the IUMG clinics and has recruited more than 2200 patients, approximately 84% of those patients contacted. With the inclusion of the private practices, PResNet has recruited over 5000 patients, approximately 85% of those patients contacted.

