Aim 3 involves the collection of pilot data and hence we may not have adequate power to detect a difference between the intervention and control groups. We will collect data on the primary outcome, the number of activities/involvements (listed in Figure 9) that a child diagnosed with an ASD is receiving and on secondary multiple patient improvement outcomes at baseline, 6 and 12 months. We will model the longitudinal data on primary outcome measured at baseline, 6 and 12 months and the change in secondary outcomes. For example, change in problem behaviors, parent stress and satisfaction at 6 and 12 months from baseline. The nature of our data is complex, a three-level data structure. The three levels are occasion of measurements, patients and clinics. Patients (level 2) are nested within clinic (level 3) and repeated measurements (level 1) are nested within patient. The model for observation  $Y_{ijk}$ , that is, observation for the  $k^{\text{th}}$  patient at time  $j$  and  $i^{\text{th}}$  clinic, is given by

$$Y_{ijk} = \alpha_{0i} + \delta_{0k} + \mathbf{X}'\boldsymbol{\beta} + \varepsilon_{ijk}$$

where the independent components

$$\alpha_{0i} \text{ distributed as } N(0, \sigma_{(3)}^2) \quad \delta_{0k} \text{ distributed as } N(0, \sigma_{(2)}^2) \text{ and} \\ \varepsilon_{ijk} \text{ distributed as } N(0, \sigma^2)$$

The random component  $\alpha_{0i}$  correlates observations within the same clinic and the random component  $\delta_{0k}$  correlates repeated observations from the same patient. The vector  $\mathbf{X}$  represents fixed covariates and  $\boldsymbol{\beta}$  represents the corresponding coefficients. We will use proc mixed available in SAS to fit this model. The fixed covariates will include treatment group, time, gender, race, age, baseline value of the response variable and other potential clinical outcomes. Baseline value of the primary outcome will not be a covariate in modeling primary outcome since the response vector ( $Y_{ijk}$ ) will include the baseline outcome. We will first test for the interaction effect between time and treatment group. If there is no interaction effect, we will evaluate the overall treatment difference. Otherwise, treatment difference will be assessed at each time point. If there is a significant difference, we will report the 95% confidence interval after adjusting for all confounding factors.

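### Aim 3 rests the adequacy of 20 children per group on a 12-per-group rule with no cluster term, although two clinics per arm leave the arm difference only imprecisely estimated

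*Protocol*

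**What the plan says.** In the Protocol, D.4 (Sample Size Calculation for Aim 3), the stated basis is estimation: "We base the sample size justification on estimation and not hypothesis testing". The size is then defended in two steps. First, "A sample size of 20 per group can be considered adequate for a pilot study". Second, the reason given is that "a sample size as low as 12 in each group provides adequate power for precision in estimating the difference between means in clinical trials". What the section means by adequate here is a matter of diminishing returns: "the gains in precision are less pronounced as sample size exceeds 12". The section gives no intraclass correlation, design effect, number of clinics or interval width.

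Three other places bear on this:

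- D (Research Design and Methods), on randomisation: "we decide to allocate two clinics to each of the study arms".
- D.3.4 (Patient Recruitment and Consent): "The same four clinics utilized in aim 2 of the study will be utilized for aim 3 of the study".
- D.4 (Sample Size Calculation for Aim 2): "This intra-cluster correlation must be taken into account in the calculation of sample size and in the analyses". Aim 2 follows this, with an intraclass correlation of 0.0082 and an inflated number per clinic.

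D.5.2 then specifies a three-level model for Aim 3 with a random effect for clinic.

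**The concern.** The diminishing-returns argument is about adding patients to each group. It describes precision well when each patient is an independent observation. In Aim 3 the randomised units are four clinics. Part of the variance of the arm difference then comes from the clinics and does not shrink as children are added, and only four units inform that part. A number of children per group cannot by itself show that the difference between means is estimated adequately.

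The protocol applies its own requirement on clustering to Aim 2 and not to Aim 3, in the same clinics. Aim 3 is meant to supply preliminary data for a larger study. Its readers need to know which quantities it will estimate usefully and which it will not.

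**Working it through.** **Inputs.** 20 children per group, two clinics per arm, and an intraclass correlation (ICC) of 0.0082 are in the Protocol. That ICC was derived for the Aim 2 screening proportion. None is given for the number of activities, so 0.05 and 0.10 are assumptions. I also assume an equal split of 10 children per clinic. Widths are in units of the total between-child SD.

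**The plan's own figures.**
- Aim 3 yield: 4000 × (1/150) × 0.80 = 21.3 per group, so the statement that more than 20 are expected reproduces, before consent and dropout.
- Aim 2: 10% against 40% with 90% power gives 49 per group with a continuity correction. Then m = (1 − 0.0082)/(4/98 − 0.0082) = 30.4, rounded up to 31 per clinic. Both reproduce.

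**The 12-per-group rule, independent children.** The 95% half-width is t(0.975, 2n − 2) × √(2/n).
- n = 6: 1.29 SD
- n = 12: 0.85 SD
- n = 20: 2.024 × √(2/20) = 0.64 SD
- n = 30: 0.52 SD

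One more child per group narrows the interval by 4.4% at 12 and by 2.6% at 20. The diminishing-returns statement therefore holds for independent children.

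**The same 20 per group in four clinics.** With the protocol's own formula, DE = 1 + ICC × (10 − 1), and Var(difference) = 2 SD² × DE/20 = 2 SD² × [ICC/2 + (1 − ICC)/20]. The half-width is t × √(2 × DE/20), with t = 2.024 on 38 patient-level df or t = 4.303 on 4 − 2 = 2 clinic-level df.

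| ICC | DE | Effective n per group | Half-width, 38 df | Half-width, 2 df |
|---|---|---|---|---|
| 0 | 1.00 | 20.0 | 0.64 SD | 1.36 SD |
| 0.0082 | 1.07 | 18.6 | 0.66 SD | 1.41 SD |
| 0.05 (assumed) | 1.45 | 13.8 | 0.77 SD | 1.64 SD |
| 0.10 (assumed) | 1.90 | 10.5 | 0.88 SD | 1.88 SD |

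**What drives the loss.** Effective n reaches 12 when 20/12 = 1 + 9 × ICC, that is at ICC = 0.074, about nine times 0.0082. The design effect at 0.0082 moves the half-width only from 0.64 to 0.66 SD. The step from 0.64 to 1.36 SD occurs even at ICC 0 and comes wholly from the 2 df.

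**Can more children repair it?** As children per clinic grow without limit, the half-width on 2 df tends to 4.303 × √ICC. At ICC 0.05 this is 0.96 SD, so the 0.85 SD benchmark cannot be reached with four clinics at 0.05 or above. At 0.0082 it takes about 65 children per group.

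**Can the clinic level be ignored?** In simulation with four clinics of 10, a patient-level 95% interval that ignores clinics covers 94.2% at ICC 0.0082, 89.7% at 0.05 and 84.0% at 0.10. It is nearly valid only if the ICC is known to be very small, which is not established for this outcome.

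**The case against.** The strongest reply is that the protocol promises little. It states no half-width, calls Aim 3 a pilot, and says in D.5.2 that power may be inadequate. The 0.64 and 0.85 SD figures are my benchmarks. This stands, and it means one cannot say that a claimed numeric precision is not met. It does not rescue the rationale: the power caveat concerns testing, while the size is defended on estimating the difference between means.

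A reader might infer that leaving out the design effect is what undermines 20 per group. The documents do not support that. At 0.0082 the effective number is 18.6, and no figure in the protocol points to an ICC above 0.074 for this outcome. Repeating Aim 2's method would give 0.66 SD, because Aim 2 uses no clinic-level df either. The protocol also names no df method, a detail commonly left to the statistical analysis plan. The wider intervals therefore rest on treating clinic as the unit of inference for the arm contrast.

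D.5.2 tests the time-by-treatment interaction first. Under the stated random-intercept model a constant clinic effect cancels from that contrast, so it is less affected. This stands, but the model has no clinic-by-time term, and the next step is the overall or time-specific arm difference, which is a contrast between clinics.

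That the 12-per-group rule assumes independent patients is inferred from its form; the cited source is not at hand.

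**Conclusion.** The point holds in a limited form. The 12-per-group rule does not show that 20 children per group is adequate for estimating the arm difference with two clinics per arm, and its use conflicts with the protocol's own requirement on clustering. With clinic-level inference, an overall or single-time arm difference has a 95% half-width of about 1.41 SD at ICC 0.0082, wider than 6 independent children per group would give. At the assumed ICCs of 0.05 and 0.10 it is 1.64 and 1.88 SD. These figures assume 10 children per clinic, 2 df and one measurement per child.

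A reader might also infer that a later trial will be mis-sized. The protocol says only that the data will help design a larger study, not that it will be sized on the observed difference, so that harm is not established. The yield arithmetic is correct, and Aim 2 and the planned three-level model are not in question here. Severity is minor to moderate.

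**What to change.** In D.4 (Sample Size Calculation for Aim 3):

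1. Remove the 12-per-group rule as the ground for adequacy.
2. State the expected 95% half-width of the arm difference with two clinics per arm, over an assumed ICC range that includes 0.0082, and name the degrees of freedom used.
3. Describe Aim 3 as feasibility and estimation of means and within-clinic SD, and say that the between-arm difference will be only imprecisely estimated.

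The cost is one paragraph and a less favourable stated property. Patient numbers and the planned model do not change.

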### **D.5 Data Analysis (Aims 2 and 3)**

For each of the two aims, baseline clinical and demographic data will be compared between the intervention and the control groups. Categorical variables will be examined using chi-square tests and continuous measures with Student's t-tests. The statistical analysis of the data will be performed using the SAS.

#### D.5.1. Data Analysis for Aim 2

The primary variable for aim 2 is whether a child at the 18 or 24-month visits was screened for ASD using the M-CHAT in the intervention group and any ASD specific screening tool in the control group. For this dichotomous outcome, we will use a non-linear mixed-effects model and will adjust for potential confounders (fixed effects) and clinic effects (random effects). To be specific, if  $Y_{ik}$  is a binary variable indicating whether the  $k^{\text{th}}$  patient in the  $i^{\text{th}}$  clinic was screened, we have

$$\log it(Y_{ik} = 1) = \alpha_i + \mathbf{X}_{ik}\boldsymbol{\beta}, \text{ where } \alpha_i \sim N(0, \varepsilon^2).$$

The random component  $\alpha_i$  correlates outcomes of patients cared by the same clinic. Physicians would not be considered as a nesting factor since the same patients at different visits may not be seen by the same physician. The vector  $\mathbf{X}_{ik}$  represents fixed covariates and  $\boldsymbol{\beta}$  represents the corresponding coefficients. The fixed covariates will include critical covariates such as treatment group, gender, and other patient and clinic level characteristics. We will also examine potential interaction terms among the covariates, particularly interactions between treatment arm and other covariates. If there is a significant treatment difference, we will report the 95% confidence interval of the treatment difference after adjusting for all confounding factors. The model will be fitted by the SAS procedure NLMIXED.

All secondary dichotomous outcomes, for example, whether a child under the age of 5 undergoes surveillance for ASDs, whether ASD surveillance led to diagnosis of ASD with an ASD specific screening tool and whether a child was referred for comprehensive ASD evaluation will also be analyzed using the same model as described above.

### D.5.2. Data Analysis for Aim 3

Aim 3 involves the collection of pilot data and hence we may not have adequate power to detect a difference between the intervention and control groups. We will collect data on the primary outcome, the number of activities/involvements (listed in Figure 9) that a child diagnosed with an ASD is receiving and on secondary multiple patient improvement outcomes at baseline, 6 and 12 months. We will model the longitudinal data on primary outcome measured at baseline, 6 and 12 months and the change in secondary outcomes. For example, change in problem behaviors, parent stress and satisfaction at 6 and 12 months from baseline. The nature of our data is complex, a three-level data structure. The three levels are occasion of measurements, patients and clinics. Patients (level 2) are nested within clinic (level 3) and repeated measurements (level 1) are nested within patient. The model for observation  $Y_{ijk}$ , that is, observation for the  $k^{\text{th}}$  patient at time  $j$  and  $i^{\text{th}}$  clinic, is given by

$$Y_{ijk} = \alpha_{0i} + \delta_{0k} + \mathbf{X}'\boldsymbol{\beta} + \varepsilon_{ijk}$$

where the independent components

$$\alpha_{0i} \text{ distributed as } N(0, \sigma_{(3)}^2) \quad \delta_{0k} \text{ distributed as } N(0, \sigma_{(2)}^2) \text{ and} \\ \varepsilon_{ijk} \text{ distributed as } N(0, \sigma^2)$$

The random component  $\alpha_{0i}$  correlates observations within the same clinic and the random component  $\delta_{0k}$  correlates repeated observations from the same patient. The vector  $\mathbf{X}$  represents fixed covariates and  $\boldsymbol{\beta}$  represents the corresponding coefficients. We will use proc mixed available in SAS to fit this model. The fixed covariates will include treatment group, time, gender, race, age, baseline value of the response variable and other potential clinical outcomes. Baseline value of the primary outcome will not be a covariate in modeling primary outcome since the response vector ( $Y_{ijk}$ ) will include the baseline outcome. We will first test for the interaction effect between time and treatment group. If there is no interaction effect, we will evaluate the overall treatment difference. Otherwise, treatment difference will be assessed at each time point. If there is a significant difference, we will report the 95% confidence interval after adjusting for all confounding factors.

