## D. Research Design and Methods

This will be a randomized trial in which we will compare changes in screening, diagnosis, and management of ASD before and after implementation of the CHICA system in intervention control practices. Although the unit of randomization will be the primary care practice, the unit of analysis will be the individual patient.

Currently, CHICA is being utilized within a purely academic setting. However, by the start of this research project, CHICA will have expanded into the community practice setting through its incorporation into pediatric clinics in the Indianapolis area that participate in the Indiana University Medical Group – Primary Care (IUMG-PC) practice network. IUMG-PC includes 14 clinic sites that cater to pediatric patients. In 2007, these clinics hosted 95,011 patient visits for children between the ages of 0 and 13. 24% of these visits were for pediatric patients with Medicaid.

For this study, we will be focusing on four of the pediatric IUMG-PC clinics that have been previously set up with the CHICA system. These four clinics see the largest number of pediatric patients within the IUMG-PC practice network. For example in 2007, these four clinics saw 8,528 patients between the ages of 0 and 3 years and 3,065 patients between the ages of 4 and 5 years. Two of the four clinics will have the ASD modules turned on; two will not and will function as the control group. This will allow us to test the impact of the specific ASD modules above that of CHICA alone. The four clinics will be ranked by their size, where size is defined by the number of physicians and residents in the clinic. A randomization plan will be used such that the first and last ranked clinics will be assigned, at random, to one group (intervention or control) and the other two clinics will be assigned to the other group.

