#### D.2.4 Data Collection

In order to evaluate the effect of the CHICA system on the screening and diagnosis of ASDs, data will be collected from two sources:

1. *Medical record abstraction.* We will use chart abstractions to assess each clinic's surveillance and screening practices related to ASDs. Research assistants (RAs) will be trained to review both the electronic medical record and paper charts for a variety of information including how often ASDs are screened for and how often surveillance is performed according to the 2007 AAP algorithm. To assess the reliability of chart abstraction, a random sample of 20% of the charts will be abstracted twice.
2. *Review of CHICA data.* Based upon information provided by physicians on the physician worksheet, CHICA will automatically collect data on the screening and diagnosis of ASD throughout the study period. Moreover, we can add questions to the pre-screener form to ask parents if their children have ever been diagnosed with an ASD.

Additionally, information about practice characteristics will be collected at baseline. The medical record abstraction and review of CHICA data will be conducted at baseline and at six-month intervals until study completion. These methods will allow a thorough description of the intervention's role in the process of ASD surveillance and screening.

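### The Aim 2 model has no period term or named baseline screening rate, so it does not estimate the before-to-after comparison that the protocol sets out

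*Protocol*

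**What the plan says.** The opening paragraph of Protocol section D describes the design: "we will compare changes in screening, diagnosis, and management of ASD before and after implementation of the CHICA system in intervention control practices". Section D.2.4 supplies the data for such a comparison: "The medical record abstraction and review of CHICA data will be conducted at baseline and at six-month intervals until study completion".

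Section D.5.1 then writes out the Aim 2 analysis: "we will use a non-linear mixed-effects model and will adjust for potential confounders (fixed effects) and clinic effects (random effects". The outcome Y_ik carries a clinic index i and a patient index k and nothing for time. On covariates it says: "The fixed covariates will include critical covariates such as treatment group, gender, and other patient and clinic level characteristics". The clinic random intercept is there because it "correlates outcomes of patients cared by the same clinic". The same model is applied to all secondary dichotomous outcomes.

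The only use of baseline data that D.5 gives for Aim 2 is a between-arm comparison of clinical and demographic variables. For Aim 3, by contrast, D.5.2 indexes time, keeps the baseline outcome in the response vector and states: "We will first test for the interaction effect between time and treatment group".

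Section D also concedes that randomising clinics carries "potential bias caused by unknown characteristics that are differentially distributed in the four clinics and related to the outcome". Its answer is to adjust for intra-cluster correlation and potential confounders.

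**The concern.** The question is posed as a difference in changes, the baseline screening data are collected, and the model for the primary hypothesis test gives them no role. The pilot aim has the time structure that the confirmatory aim lacks.

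This matters because only four clinics are randomised. Clinics are ranked by size, with first and last forming one pair and the middle two the other, so there are just two possible allocations. Which clinics share an arm is fixed by size; chance decides only which pair gets the module. Treatment is constant within a clinic over follow-up, so in follow-up data alone a lasting difference between the pairs cannot be told apart from a module effect. A random intercept can widen the standard error but cannot take that difference out of the point estimate. Each clinic's own earlier screening rate is the most direct handle on it.

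**Working it through.** **Inputs.** From D.4.1 (Aim 2): assumed baseline clinic rates 6, 8, 10, 12%; planned rates 10% (control) and 40% (intervention); alpha 0.05; power 90%; effective n 49 per group; intra-class correlation 0.0082; 31 children per clinic; at least 1000 eligible visits a year, 3000 over three years. An even spread over clinics (750 each) is my assumption.

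**1. The plan's own figures reproduce.** A two-sided comparison of 10% with 40% at 90% power needs 42 per group, or 49 with continuity correction. Then m = (1 − 0.0082)/(4/98 − 0.0082) = 0.9918/0.0326 = 30.4, rounded up to 31. This sizing is for a single between-arm comparison of proportions, not for a change.

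**2. Arm differences with no module effect.**

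| Pairing | Arm means | Difference | Odds ratio |
|---|---|---|---|
| 6+12 vs 8+10 | 9% vs 9% | 0 | 1.00 |
| 6+10 vs 8+12 | 8% vs 10% | 2 points | 1.28 |
| 6+8 vs 10+12 | 7% vs 11% | 4 points | 1.64 |

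**3. Worst split with a true 30-point rise in the module arm and no change in control.**
- Module arm starts at 7%: follow-up 37% vs 11%, so 26 points (odds ratio 4.75).
- Module arm starts at 11%: follow-up 41% vs 7%, so 34 points (odds ratio 9.23).
- Change contrast: (37 − 7) − (11 − 11) = 30 and (41 − 11) − (7 − 7) = 30.
- On the logit scale the change contrast is a ratio of odds ratios, 7.80 or 5.62. These differ because a constant 30-point rise is not a constant odds ratio.

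**4. Does the random intercept remove the difference?** The stated model was simulated on the 4-point split with no module effect (200 runs per setting). The median module odds ratio was 1.69 at 31 per clinic and 1.66 at 750 per clinic, against 1.64 built in, so it does not. A large-sample likelihood ratio test rejected in 9% and 71.5% of runs respectively. Small-sample degrees of freedom would lower both figures.

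**5. Price of using the baseline.**
- Standard error of the baseline arm difference at 7% vs 11%: √[(0.07×0.93 + 0.11×0.89)/n], with n per arm. For n = 62 (31 per clinic) it is 5.1 points, more than the 4 points being removed. For n = 250 (125 per clinic, i.e. 1000/4/2 for six months) it is 2.6 points.
- Effective n per arm per period for a 30-point change contrast: (1.96 + 1.2816)² × (3×0.09 + 0.24)/0.30² = 59.5, so 60, or 240 over four cells. The protocol plans 98 in total. By the same unpooled formula, the follow-up-only comparison needs 38.5, so 39 per arm.
- Clinic-level t test on 2 df, simulated with 10% at baseline in every clinic, a 30-point effect and no clinic-by-period variance: at 31 children per clinic per period, power is about 45% for changes and about 60% for follow-up rates alone. With 3000 visits in seven equal windows (107 baseline and 643 follow-up per clinic), power for changes is about 98%.
- With those larger numbers, on the 4-point split with no module effect, the change test rejects in 5% of runs and the same t test on follow-up rates in 17%.

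**The case against.** **The opening sentence is loose.** It refers to implementing CHICA, which all four clinics already have, and its last words are garbled. Elsewhere the contrast is the ASD modules over CHICA alone, and D.2.5, D.4.1 and D.5.1 treat the primary outcome as a proportion compared between arms. This is fair and lowers the weight of the contradiction. It does not explain why screening is abstracted at baseline and then given no analytic role in Aim 2.

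**The covariate list is open-ended.** Clinic characteristics could include the baseline screening rate, and interactions with arm are to be examined. That stands as a possibility, but neither period nor baseline rate is named. Adjusting for the baseline rate would be a legitimate alternative, though at clinic level an intercept, an arm effect and one covariate leave one degree of freedom from four clinics.

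**The imbalance is modest and random in direction.** This also stands. If screening rate tracks clinic size, the planned pairing gives the 0-point split, although the protocol does not show that it does. The random intercept is intended to carry clinic variation into the standard error, and at the planned 31 per clinic even the worst split rejected in only 9% of runs.

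**Two stronger readings are not supported.** A reader might infer that baseline visits will be pooled with follow-up visits under the arm label, diluting the effect. Nothing in the protocol says that pre-implementation visits enter the model. A reader might also infer a systematic bias towards the module. Allocation of the pairs is random, so either arm is equally likely to start higher.

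**Conclusion.** The point holds as a mismatch between the stated comparison, the data collected and the Aim 2 model. It should be fixed, but it does not threaten the main conclusion by itself. On the protocol's assumed rates the distortion is 0, 2 or 4 points against a planned 30, so the worst case is an estimate of 26 or 34. The 4-point figure is the worst of three splits, and the four rates are planning assumptions, not observations; true clinic differences are unknown. The same few points would matter more for secondary dichotomous outcomes with smaller effects. The 71.5% rejection figure should not be read as the trial's error rate: it assumes the worst split, 750 children per clinic and a large-sample test.

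**What to change.** In D.5.1, define a baseline window before the module is switched on, index 18- and 24-month visits by period, add period and arm-by-period terms, and name the arm-by-period contrast as the primary Aim 2 effect. A period main effect alone would not be enough. Clinic-by-period variation is desirable in principle but is barely estimable from eight clinic-period cells, so the inference should be a small-sample one.

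A separate and simpler option, on the risk-difference scale, is to compute each clinic's follow-up rate minus its baseline rate and compare the two arms' mean changes with a t test on 2 df. The two options target different effect measures, so one must be chosen in advance. Apply the same approach to secondary outcomes that have baseline abstraction.

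No new data source is needed. The cost is baseline sampling noise, which is prohibitive at 31 children per clinic and small if the available visits (about 1000 a year across the clinics) are used in each period. That means more abstraction than the present sample size implies, and the sample-size text in D.4.1 must be restated for the change contrast.
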